### **6.4.2. Benefits**

Intermittent use of nebulized tobramycin is indicated for the long-term management of chronic pulmonary infection due to *P. aeruginosa* in CF patients aged 6 years and older (SPC TOBI®). Several studies (see paragraph 6.3) showed that treatment with inhaled tobramycin might also be beneficial to patients with non-CF bronchiectasis whom are colonized by *P. aeruginosa*. Long-term intermittent administration appears to be safe and lessen disease severity.

Benefits of administering tobramycin by use of the DPI instead of by nebulisation are a less time consuming and easier drug administration that is less of a burden on the patient's (social) life and no pollution of the environment. Furthermore, because it is a single-use device there is no need for hygiene control or maintenance of the equipment and no risk of device contamination and patient (re)infection.

### **6.5 Description and justification of route of administration and dosage**

The way of administration will be as dry powder using a DPI. Further information about the technical aspects of the DPI see section *The dry powder inhaler* in the Introduction and rationale. This device can generate high volumes of dry powder, needed for a substance and with an aim like tobramycin.

### **6.6 Dosages, dosage modifications and method of administration**

In a study with CF patients 112 mg of dry powder tobramycin using the Podhaler was comparable with 300 mg of tobramycin via nebulisation, which is the recommended clinical dose in this population. However for patients with non-CF bronchiectasis no optimal dosage has been studied.

Based on the in vitro data analysis, we expect that a lower dose of DP tobramycin using the Cyclops® will result in similar deposition characteristics with similar pharmacokinetic parameters compared to DP tobramycin using the Podhaler. Since, the Cyclops® has a higher inhaler resistance than the Podhaler®, the airflow through the Cyclops® (at the same pressure drop) will be lower and this will result in a more efficient lung deposition and thus, we expect that a lower tobramycin dose will result in the same plasma levels as the Podhaler® dose of 112 mg. To test this hypothesis it's not necessary to incorporate a DP Tobramycin dose of 112 mg in the Cyclops®, because the inhalers and the formulations are very different. Furthermore, the Cyclops® is optimised to disperse 30 mg of DP Tobramycin (blisters contain 30 mg), therefore the doses chosen are 30, 60, 120 and 240 mg. Two dosages are below the Podhaler dosage, one is more or less comparable with the current dosage of the Podhaler and the last dose is higher than the

dosage of the Podhaler to study the local tolerability of the Cyclops® in case of an overdose. This last dose (240 mg) is generally considered safe, and it is still lower than the dose given normally as first dose intravenously in patients with sepsis of unknown origin.

#### **6.6.1. Dosages:**

We will do an ascending dose response study with 4 different doses (30, 60, 120 and 240 mg). The doses will be fixed rising to react to possible adverse events and a possible end of the study for the participant.

#### **6.6.2. Method of administration:**

Tobramycin will be administered by inhalation using a DPI, called the Cyclops®. The DPI has been developed at the department of Pharmaceutical Technology and Biopharmacy of the University of Groningen.

#### **6.6.3. Justification of the new dry powder inhalation device, the Cyclops®**

Aminoglycosides (like tobramycin) are very hygroscopic. The delivery with re-usable capsule inhalers can cause particles to retain within the inhaler, which can absorb moisture from the air and stick firmly to the inhaler walls and this can influence following inhalations.

The Cyclops® is designed as a disposable device with a high inhaler resistance to reduce the flow rate, and thus, the speed of entry of the tobramycin particles. This will significantly reduce the mouth and throat deposition, and increase the dose fraction available for deposition in the lungs.

To reach the highest deposition in the peripheral airways (94% of total lung volume is in the generations 17 to 23), the total dose has to enter the airways within the first 0.5 to 1 L of air inhaled. When the emission time is longer than two seconds at a flow rate of 30 L/min, more than 1 L of air has to be inhaled to take the entire dose. The emission time from the Cyclops® is less than 2 seconds. Table 3 shows that the dispersion efficiency of the Cyclops®.

The formulation used in the Cyclops® consists of 100 per cent tobramycin. Because this inhaler was specifically designed for tobramycin, no excipients are needed to disperse the formulation. Moreover, because no excipients are needed, a single blister can contain a much higher fraction of the total drug dose.

In conclusion, the specific design of the Cyclops® with the high inhaler resistance (that prevents high mouth and throat deposition), and the patented air classifier technology, will result in an efficient dispersion, and thus probably in a more efficient therapy.

**Table 3:** Dispersion efficiency of the Cyclops® and TOBI® Podhaler® at a flow rate of 30 L/min.

|                      | Cyclops® tobramycin
50 mg dose (=50 mg tobra)
30 L/min. | TOBI® Podhaler®
45.5 mg dose (=28 mg tobra)
30 L/min. |
|----------------------|---------------------------------------------------------------|-------------------------------------------------------------|
| X 10 (µm) | 1.75                                                          | 1.94                                                        |
| X 50 (µm) | 3.26                                                          | 3.95                                                        |
| X 90 (µm) | 6.38                                                          | 9.71                                                        |

## 6.7 Preparation and labelling of Investigational Medicinal Product

### *Preparation:*

A solution of 50 mg/mL tobramycin in water for injections was spray dried with a Büchi Mini B-290 spray dryer. The spray dried product was transferred to a freeze-dryer (Christ, Epsilon 2-4) to remove residual water. Tobramycin is very hygroscopic and water can cause the formation of agglomerates, which can negatively affect powder dispersion properties.

### *Filling:*

Aluminum blisters were filled with 30 mg of tobramycin and 10 mg of α-lactose monohydrate sweeper crystals (Ph.Eur. quality; DMV Fonterra Excipients, Goch, Germany) to obtain the final DP Tobramycin product.

### *Sealing:*

The blisters are sealed thermally with standard sealing equipment. The seal is formed between a PVC coating on the aluminum blister and a heat lacquer (suitable for PVC) on the aluminum foil strip by heating to around 200 °C for a few seconds.

### *Labelling:*

Labels will contain the following information:

- a) name, address and telephone number of the investigator;
- b) pharmaceutical dosage form, route of administration, quantity of dosage units;
- c) the batch number;
- d) a trial reference code;

- e) “for clinical trial use only” or similar wording;
- f) the storage conditions;
- g) expiry date.

### **6.8 Drug accountability**

Drug accountability will be performed according GCP guidelines and performed by the investigator and the Hospital Pharmacy.

## 7. METHODS

### 7.1 Study parameters/endpoints

#### 7.1.1 Main study parameter/endpoint

The following pharmacokinetic parameters will be calculated:

- Actual dose (dose minus remainder in inhaler after inhalation)
- AUC0-12 (area under the curve from 0 -12 h)
- Cmax (maximum plasma concentration)
- Tmax (time to maximum plasma concentration)
- Ka absorption rate constant
- T1/2 el terminal elimination half-life
- CL/F clearance following pulmonary administration (F= bioavailability)

Local tolerability of the inhalation of dry powder tobramycin. Both points need to have a positive result.

- Drop of FEV1 of >10% (lung function measurement)
- Adverse events

### 7.2 Randomisation, blinding and treatment allocation

Not applicable

### 7.3 Study procedures

#### 7.3.1 Pharmacokinetic analysis

Pharmacokinetic analysis is studied using software suitable for population pharmacokinetic modeling (i.e. MW/Pharm NonMem).

#### 7.3.2 Actual inhaled dose

After inhalation the inhaler will be tested for the amount of drug remaining in the device. The device will be rinsed with water and the remaining tobramycin will be determined using a modification of the 2,4,6-Trinitrobenzene Sulfonic Acid (TNBSA) assay. The actual inhaled dose of tobramycin will be calculated by subtracting the amount of drug remaining in the device after inhalation from the total dose weighed into the device.

#### 7.3.3 Blood sampling and analysis:

Venous blood samples will be collected after inhalation of tobramycin from an infusion needle. Serum samples will be collected directly before and after 15 minutes, 30 minutes, 45 minutes, 1 h, 1¼ h, 1½ h, 1¾ h, 2 h, 4 h, 8 h and 12 h after inhalation. These samples

will be centrifuged immediately and the serum will be stored at -20°C during the sampling day (UMCG, Haren). After shipment to the UMCG (Groningen) samples will be stored at -80°C until analysis.

#### **7.3.4 Gastro-intestinal absorption of tobramycin**

From the literature it is expected that the gastro-intestinal absorption of tobramycin is far less than 1%. Therefore, we will not test the gastro-intestinal absorption in this group of subjects.

#### **7.3.5 Serum creatinin analysis**

Serum creatinin will be determined in the routine UMCG central lab.

#### **7.3.6 Creatinin clearance**

Will be calculated using the formula of Cockcroft-Gault

#### **7.3.7 Adverse effects**

Spirometry will be used to test for adverse broncoconstrictive reactions due to the inhalation, immediately before, 15, 30 and 90 minutes after inhalation. It will be performed by standardized procedure according to the ERS guidelines and reference values. A 10% or more decrease in FEV1 (in mL) will be considered clinically relevant.

Other adverse effects will be asked by the investigator for spontaneous reporting. Special attention will be for cough and dyspnea.

#### **7.3.8 X-ray of the chest**

Before the start of the study a X-ray of the chest will be made of the patients who haven't had one the last year before screening for this study. This is both to find no existing abnormalities before start of the study and to have a reference in case an adverse event has happened.

#### **7.3.9 Inhalation flow measurement**

Prior to inhalation the patients will receive inhalation instructions and the opportunity to practice the inhalation manoeuvre. This will be done by using an empty inhaler connected to an electronic inspiratory flow measurement device (University of Groningen). With this device inhalation flow curves will be recorded and as soon as a series of consistent maneuvers is obtained, the Cyclops® containing tobramycin is given to the patient for administration of the drug. During the inhalation of tobramycin the inspiratory flow will be measured as well.

## **7.4 Withdrawal of individual subjects**

Subjects can leave the study at any time for any reason if they wish to do so without any consequences. The investigator can decide to withdraw a subject from the study for urgent medical reasons.

### **7.4.1 Specific criteria for withdrawal**

Special criteria for withdrawal include an allergic or anaphylactic reaction to tobramycin, and drop in  $FEV_1 > 10\%$ , cough or dyspnoea in direct relation to the inhalation given the rising dose administration.

## **7.5 Replacement of individual subjects after withdrawal**

If a subject withdraws him or herself, he or she will be replaced in order to reach the number of subjects needed for this study.

## **7.6 Follow-up of subjects withdrawn from treatment**

Follow-up will be done by their chest physician or their general practitioner

## **7.7 Premature termination of the study**

The criteria for terminating the study prematurely are a high percentage of adverse events like allergic reactions, and a high number of withdrawals for whatever reason.

## 8. SAFETY REPORTING

### 8.1 Section 10 WMO event

In accordance to section 10, subsection 1, of the WMO, the investigator will inform the subjects and the reviewing accredited METC if anything occurs, on the basis of which it appears that the disadvantages of participation may be significantly greater than was foreseen in the research proposal. The study will be suspended pending further review by the accredited METC, except insofar as suspension would jeopardise the subjects' health. The investigator will take care that all subjects are kept informed.

### 8.2 AEs, SAEs and SUSARs

#### 8.2.1 Adverse events (AEs)

Adverse events are defined as any undesirable experience occurring to a subject during the study, whether or not considered related to [the investigational product / the experimental intervention]. All adverse events reported spontaneously by the subject or observed by the investigator or his staff will be recorded.

#### 8.2.2 Serious adverse events (SAEs)

A serious adverse event is any untoward medical occurrence or effect that at any dose:

- results in death;
- is life threatening (at the time of the event);
- requires hospitalisation or prolongation of existing inpatients' hospitalisation;
- results in persistent or significant disability or incapacity;
- is a congenital anomaly or birth defect;
- Any other important medical event that may not result in death, be life threatening, or require hospitalization, may be considered a serious adverse experience when, based upon appropriate medical judgement, the event may jeopardize the subject or may require an intervention to prevent one of the outcomes listed above.

The sponsor will report the SAEs through the web portal *ToetsingOnline* to the accredited METC that approved the protocol, within 15 days after the sponsor has first knowledge of the serious adverse reactions.

SAEs that result in death or are life threatening should be reported expedited. The expedited reporting will occur not later than 7 days after the responsible investigator

has first knowledge of the adverse reaction. This is for a preliminary report with another 8 days for completion of the report.

### **8.2.3 Suspected unexpected serious adverse reactions (SUSARs)**

Adverse reactions are all untoward and unintended responses to an investigational product related to any dose administered.

Unexpected adverse reactions are SUSARs if the following three conditions are met:

1. the event must be serious (see chapter 9.2.2);
2. there must be a certain degree of probability that the event is a harmful and an undesirable reaction to the medicinal product under investigation, regardless of the administered dose;
3. the adverse reaction must be unexpected, that is to say, the nature and severity of the adverse reaction are not in agreement with the product information as recorded in:
  - Summary of Product Characteristics (SPC) for an authorised medicinal product;
  - Investigator's Brochure for an unauthorised medicinal product.

The sponsor will report expedited the following SUSARs through the web portal *ToetsingOnline* to the METC:

- SUSARs that have arisen in the clinical trial that was assessed by the METC;
- SUSARs that have arisen in other clinical trials of the same sponsor and with the same medicinal product, and that could have consequences for the safety of the subjects involved in the clinical trial that was assessed by the METC.

The remaining SUSARs are recorded in an overview list (line-listing) that will be submitted once every half year to the METC. This line-listing provides an overview of all SUSARs from the study medicine, accompanied by a brief report highlighting the main points of concern.

The expedited reporting of SUSARs through the web portal *ToetsingOnline* is sufficient as notification to the competent authority.

The sponsor will report expedited all SUSARs to the competent authorities in other Member States, according to the requirements of the Member States.

The expedited reporting will occur not later than 15 days after the sponsor has first knowledge of the adverse reactions. For fatal or life threatening cases the term will be maximal 7 days for a preliminary report with another 8 days for completion of the report.

### **8.3 Annual safety report**

As we expect to end this study within one year, a safety report will be submitted after the study is ended to the accredited METC, competent authority, Medicine Evaluation Board and competent authorities of the concerned Member States.

This safety report consists of:

- a list of all suspected (unexpected or expected) serious adverse reactions, along with an aggregated summary table of all reported serious adverse reactions, ordered by organ system, per study;
- a report concerning the safety of the subjects, consisting of a complete safety analysis and an evaluation of the balance between the efficacy and the harmfulness of the medicine under investigation.

### **8.4 Follow-up of adverse events**

All AEs will be followed until they have abated, or until a stable situation has been reached. Depending on the event, follow up may require additional tests or medical procedures as indicated, and/or referral to the general physician or a medical specialist. SAEs need to be reported till end of study within the Netherlands, as defined in the protocol

### **8.5 Data Safety Monitoring Board (DSMB) / Safety Committee**

Will not be established for this very short time, 8 subject study of a new device but with a well known drug.

## 9. STATISTICAL ANALYSIS

### 9.1 Descriptive statistics

Descriptive statistics will be used for calculation (geometric) mean and (interquartile) range of observed age, weight, length, dose, clinical parameters, (unbound)  $AUC_{0-24h}$ , and  $C_{max}/MIC$  ratio, (unbound)  $AUC_{0-24h}/MIC$ ,  $T_{max}$ ,  $C_{max}$ ,  $T_{1/2}$  will be calculated with a 95% confidence interval. The other end-point will be proportions of subjects reporting adverse effects on all treatment days and / or percentage of drop of FEV1 of more than 10%.

### 9.2 Inferential statistics

Univariate analysis will be used to test if co-variables, including sex, ethnicity, co-morbidity, medical history, dose and duration of (TB) and co medication have an effect on PK parameters like  $T_{max}$ ,  $C_{max}$  and the (unbound)  $AUC_{0-24h}$  of tobramycin. Differences in clinical parameters between baseline and end of study will be calculated. When not normally distributed, non-parametric tests were used, i.e. Mann-Whitney  $U$  test and Wilcoxon rank sum test for ordinal data and Chi square tests will be used for nominal data. Correlation coefficients (Spearman's or Pearson's depending on distribution) will be used to test

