### 5.4 Sample size calculation

We assume to need eight participants for this study. A specific calculation of the number of subjects needed is difficult, but low numbers have provided good results in other dry powder inhalation studies of antibiotics: A single dose study with dry powder inhalation of colistin for cystic fibrosis (CF) patients by LeBrun et al was performed with 5 patients. Another single dose study with dry powder colistin inhalation by Westerman et al was performed with 10 CF patients. Geller et al performed a single dose with a dose escalation study of dry powder tobramycin inhalation with 12 CF patients in each dose escalation arm. Each arm inhaled a fixed dose. Newhouse et al did a 5 period study with technetium labeled dry powder tobramycin with 14 healthy volunteers. First 3 periods were single dose. The last period was a 6-fold dose. Pilcer et al performed a single dose study with dry powder tobramycin inhalation in 9 CF patients. Therefore, we expect the 8 subjects in our single ascending dose study to be sufficient.

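### Section 9.2 lets the observed distribution choose the test and the correlation coefficient, and 9.1 leaves the type of mean open; with eight patients both should be fixed in advance

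*Protocol*

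**What the plan says.** - **Choice of test (Protocol 9.2).** The section opens with univariate tests of whether covariates "have an effect on PK parameters like" Tmax, Cmax and AUC. It next mentions changes in clinical parameters over the study, and then says "When not normally distributed, non-parametric tests were used". The rank tests follow, with chi-square tests for nominal data. No normality check or threshold is named.
- **Choice of correlation (Protocol 9.2).** The coefficient is "Spearman's or Pearson's depending on distribution".
- **Summaries (Protocol 9.1).** The text reads "Descriptive statistics will be used for calculation (geometric) mean and (interquartile) range of observed age, weight, length, dose, clinical parameters", and the same sentence goes on to the PK measures, including Tmax, with a 95% confidence interval. The words for geometric and interquartile stand in brackets, so the type of mean and range is left open.
- **Scale.** No section fixes a log scale for any PK parameter. Section 7.3.1 names only population-PK software.
- **Size and design.** Section 5.4 says "We assume to need eight participants for this study". Section 6.6.1 gives each patient four ascending doses, from 30 to 240 mg.

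**The concern.** A rule that reads the method off the data is useful only if the data can show what the rule asks. Eight values say little about shape, and concentrations and exposures are usually right-skewed. Such a rule would mostly return 'normal' for skewed data, and would return 'not normal' now and then by chance. The same parameter in the same patients could therefore be handled by different methods in different analyses without any true difference in shape.

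At stake are the validity of the covariate tests and correlations in 9.2 and the accuracy of any raw-scale interval reported under 9.1. Pharmacokinetics is a primary objective (section 3), so it is worth settling the scale before results are seen.

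**Working it through.** The protocol gives no error rate, power or standard deviation, and section 5.4 says of the sample size that "A specific calculation of the number of subjects needed is difficult". There is thus no planned figure to reproduce, and the rule was checked by simulation.

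**Inputs from the protocol:** n = 8 (5.4); four doses of 30, 60, 120 and 240 mg in the same patients (6.6.1); method chosen by distribution (9.2).

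**Assumptions not in the protocol:** lognormal values; Shapiro-Wilk at 5% as the check; CV of 40% to 80%; within-patient correlation of 0.8 on the log scale. The log-scale SD is σ = √ln(1 + CV²), which is 0.385 at CV 40% and 0.703 at CV 80%.

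**Step 1, detection.** Proportion of samples of eight lognormal values with p < 0.05.

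**Step 2, disagreement across doses.** Proportion of trials in which the check rejects at one, two or three of the four doses, although the true shape is the same at all of them.

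**Step 3, coverage.** Mean ± t(0.975; 7 df) × SD/√8. On the raw scale the target is the arithmetic mean, and on the log scale it is the geometric mean.

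| CV | Flagged as non-normal | Mixed verdicts, correlation 0.8 | Raw-scale coverage | Log-scale coverage |
|---|---|---|---|---|
| 40% | 12.9% | 34.2% | 93.1% | 94.9% |
| 50% | 17.5% | 39.6% | 92.3% | 95.1% |
| 60% | 21.4% | 45.8% | 91.3% | 95.0% |
| 80% | 30.3% | 54.8% | 89.0% | 95.1% |

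Repeat runs move the first two result columns by one or two percentage points, hence the rounded ranges of 13% to 31% and 34% to 56%. On truly normal data the check rejects in 5.2% of samples, as it should.

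**Cross-check of step 2.** With independent doses, the chance of mixed verdicts is 1 − p⁴ − (1 − p)⁴. At CV 40%, p = 0.129 gives 1 − 0.0003 − 0.5755 = 0.424, against 0.433 simulated at zero correlation. Positive correlation lowers this to 0.342, as expected.

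**Step 4, pooled doses.** If all 8 × 4 = 32 values are checked together, the dose range of 240/30 = 8 dominates. With exposure proportional to dose, the check rejected in 98% to 100% of trials at CV 20% to 60%, even when values were exactly normal within each dose. It then detects the dose design and not the shape of the parameter.

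**The case against.** The strongest reply is that the text of 9.2 is narrow, and much of this stands.

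- **Scale of the summaries.** A reader might infer that arithmetic or geometric mean is also chosen from how the data look. The documents do not say so. Section 9.2 ties only the test and the correlation coefficient to the distribution, and 9.1 merely leaves the mean open.
- **Effect on the next study.** A reader might infer that the exposure estimate used to choose the next regimen (end of section 2) hangs on a chance decision. That is not supported. The tests in 9.2 screen covariates and clinical changes. The exposure summaries come from 9.1 and the modelling in 7.3.1, and the dose-AUC analysis in 9.3 has no normality switch.
- **Check per dose.** Nothing says that normality is judged at each dose. Dose is itself a listed covariate, which points towards pooling for that analysis. The mixed-verdict figures are therefore conditional. Pooling does not rescue the rule, as step 4 shows.
- **Two kinds of mean.** The arithmetic mean of lognormal data exceeds the geometric mean by a factor of √(1 + CV²). This is a difference in what is estimated, not an error, and I do not count it as harm.
- **Tmax.** Only an observed Tmax is confined to the sampling times in 7.3.3 (every 15 minutes to 2 h, then 4, 8 and 12 h). A model-derived Tmax would be continuous, and the protocol does not say which is meant.
- **Left to an analysis plan.** The form of summaries often is. An explicit rule that the data decide is not silence, however, and can be reviewed as written.

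**Conclusion.** The point holds in limited form. Section 9.2 fixes a data-dependent choice of test and correlation coefficient that eight patients cannot support, and 9.1 leaves the type of mean open. Under the stated assumptions the check misses the skewness in roughly 70% to 87% of samples (100% minus 30.3% and 12.9%). It gives inconsistent answers if used per dose and an uninformative one if doses are pooled. Where the raw scale is used, a nominal 95% interval falls short by about 2 to 6 percentage points.

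The figures rest on lognormal shape, Shapiro-Wilk at 5%, CVs of 40% to 80% and, for the mixed verdicts, per-dose checking with a correlation of 0.8. The 95% coverage on the log scale follows from assuming lognormal data. At lower CVs the loss is smaller: raw-scale coverage is 94.3% at CV 20%. Severity is minor to moderate, since the study is small and mainly descriptive.

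**What to change.** Amend 9.1 and 9.2 to state that:

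- AUC, Cmax, CL/F and half-life are always analysed as logarithms and reported as geometric mean, geometric CV and back-transformed 95% confidence interval;
- correlations and covariate tests for these parameters use the log values;
- observed Tmax is summarised as median and range and tested by rank methods;
- no normality check decides the method for any parameter, so the clinical parameters covered by the same rule each need one named method.

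This costs a few sentences and needs no extra patients, samples or data. It should be done before the concentration results are seen.

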#### **4. STUDY DESIGN**

The study will be a single centre, single ascending, single dose study of inhaled dry powder tobramycin as a first step to investigate the pharmacokinetics of four doses with no more local intolerability than when tobramycin is administered by nebulisation. The study includes 8 patients with non-CF bronchiectasis who meet the in- and exclusion criteria. These 8 patients will be recruited from the outpatient department of pulmonology.

See tables 1 and 2 for interventions and a timetable

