## 12.2 Synthesis

The study design is chosen as such to minimize the chance on the occurrence of an adverse event. The starting dose is much lower than the dose given with TOBI Podhaler®, because we expect that the fraction of the dose deposited in the lungs is higher for our device than for the TOBI Podhaler®. The doses will be administered in a rising order to be able to react to possible adverse events and to possibly end the study prematurely for the participant if necessary. During this study DP Tobramycin will only be administered in a hospital setting, so in case of an emergency adequate action can be taken (e.g. salbutamol for bronchoconstriction).

DP Tobramycin contains only tobramycin and lactose, both compounds that are approved for pulmonary administration. Furthermore, tobramycin has been used for long-term therapy for decades already. The long term risks for tobramycin, predominantly nephrotoxicity and ototoxicity, are due to prolonged exposure to and cumulation of the compound in these organs. In this study, a patient receives four individual doses in four weeks, and no chronic therapy. To reduce the risk of interaction with other drugs, we will screen for cyclosporin, cisplatin, amfotericin B, cephalosporins, polymyxins, vancomycin and NSAIDs. Use of these products should be ceased if possible (NSAIDs), otherwise the patient cannot participate in the study. Therefore, we conclude that the long term risks are negligible.

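### Section 9.2 names only independent-sample tests, although every time or dose contrast in this single group of eight is within patient

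*Protocol*

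**What the plan says.** Section 4 describes one group: "The study includes 8 patients with non-CF bronchiectasis who meet the in- and exclusion criteria". Section 7.2, on randomisation and allocation, reads "Not applicable". Table 2 takes each patient through 30, 60, 120 and 240 mg at successive visits, and section 12.2 confirms it: "In this study, a patient receives four individual doses in four weeks, and no chronic therapy". Section 7.3.7 has spirometry immediately before and three times after each inhalation.

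Section 9.2, headed Inferential statistics, contains three steps in this order:

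1. Covariates against PK parameters: "Univariate analysis will be used to test if co-variables, including sex, ethnicity, co-morbidity, medical history", with dose and co-medication later in the same list.
2. Change over time: "Differences in clinical parameters between baseline and end of study will be calculated".
3. Choice of test: "When not normally distributed, non-parametric tests were used", followed by Mann-Whitney U and "Wilcoxon rank sum test for ordinal data and Chi square tests will be used for nominal data".

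No signed-rank, McNemar, Friedman, paired t or mixed-model analysis is named in sections 9.1 to 9.3.

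**The concern.** Mann-Whitney U and Wilcoxon rank sum are two names for the same test of two independent samples. The chi-square test of a two-by-two table also assumes that the two rows come from different people. Here the only contrasts over time or dose (baseline to end of study, before to after inhalation, one dose to the next) compare patients with themselves. The named tests come straight after the sentence on baseline-to-end differences, so an analyst following the text would naturally apply them there.

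This is not a matter merely left to a statistical analysis plan: the protocol chooses specific tests, and they do not match the design. With 8 patients, pairing is the main source of precision, and an unpaired test discards it. P-values for within-patient change would be wrong, in a direction that depends on the type of outcome.

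**Working it through.** **Inputs.** From the protocol: n = 8, one group, four doses per patient. The protocol states no significance level for tests, no SD, no effect size and no within-patient correlation (rho), and section 5.4 derives no sample size, so there is no stated figure to reproduce. Assumptions: two-sided 5%, bivariate normal data with equal SD, rho from 0 to 0.9, and shifts measured in between-patient SDs.

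**Why the unpaired test goes wrong.** With SD σ, an unpaired analysis judges the mean difference against a variance of 2σ²/n. The actual variance of a within-patient mean difference is 2σ²(1 − rho)/n. At rho = 0.8 the reference variance is 1/(1 − 0.8) = 5 times too large, so the test rejects too rarely.

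**Continuous or ordinal outcomes.** Exact tests were simulated on 8 pairs, 200,000 replicates per setting. The signed-rank test cannot reach exactly 5% at n = 8. It rejects when the smaller rank sum is at most 3, which 5 of the 2⁸ = 256 sign patterns give in each tail: 2 × 5/256 = 3.9%.

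| rho (assumed) | True size, rank sum | True size, signed-rank | Power at 0.8 SD, rank sum | Power at 0.8 SD, signed-rank |
|---|---|---|---|---|
| 0 | 5.0% | 3.9% | 31% | 24% |
| 0.3 | 2.4% | 3.8% | 28% | 32% |
| 0.5 | 1.2% | 3.9% | 27% | 43% |
| 0.7 | 0.4% | 3.9% | 25% | 64% |
| 0.8 | 0.1% | 3.8% | 25% | 81% |
| 0.9 | 0.02% | 3.9% | 24% | 98% |

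As a share of signed-rank power, the rank sum test keeps 27/43 = 63% at rho 0.5, 25/64 = 39% at 0.7 and 25/81 = 31% at 0.8. At rho 0 it is the more powerful of the two.

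**Yes/no outcomes.** Take no events at baseline and b of 8 at the end, all changes one way. With N = 16 observations:

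- b = 5, chi-square: 16 × (8 × 5)² / (8 × 8 × 5 × 11) = 25,600/3,520 = 7.27, p = 0.007.
- b = 5, Yates: 16 × (40 − 8)² / 3,520 = 4.65, p = 0.031.
- b = 5, exact McNemar: 2 × 0.5⁵ = 0.063.
- b = 4: chi-square 5.33, p = 0.021; Yates 3.0, p = 0.083; exact McNemar 2 × 0.5⁴ = 0.125.

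Expected event counts are 5/2 = 2.5 and 4/2 = 2 per row, below the usual minimum of 5. For this pattern, plausible for adverse events, chi-square overstates the evidence. Part of that comes from the large-sample approximation and part from ignoring the pairing.

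**The case against.** The strongest reply is about wording. The baseline-to-end differences are to be calculated; the text does not say outright that they will be tested. The only testing stated before the test list concerns covariates and PK parameters, and for sex or ethnicity an independent-sample test is right. That reading is available, and a reader who concludes that the protocol definitely tests change over time with unpaired tests goes further than the text. It does not clear the section, however. The heading is inferential, the test list follows the change sentence directly, and the covariate list includes dose, which varies within patient. Even for sex, the tests are valid only with one value per patient, which is not stated. It is also possible that signed-rank was meant where rank sum was written, since naming one test twice serves no purpose, but the document does not say so.

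A reader might infer that most of the power is lost. That depends on a correlation the protocol does not give: it is true for a 0.8 SD shift from about rho 0.7 upward, but not at 0.5, and at 0 there is no loss. High correlation is plausible for repeated FEV1 in one patient, but the clinical parameters are not defined. Nor does the power argument extend to chi-square, which errs the other way in the examples above.

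A reader might also infer that a real fall in FEV1 would be missed and the tolerability conclusion put at risk. The document does not support this. Tolerability rests on an FEV1 threshold and adverse events (7.1.1, 7.3.7), reported as proportions under 9.1, and withdrawal is judged patient by patient (7.4.1). No stated endpoint, stopping rule or sample size depends on these p-values.

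**Conclusion.** The point holds at moderate severity. Section 9.2 names tests for independent samples, while the design yields only paired contrasts over time and dose. If the tests are applied to those contrasts, the rank sum test is too conservative whenever rho is clearly above 0: true size falls from about 5% at rho 0 to 1.2% at 0.5 and 0.1% at 0.8, while signed-rank stays near 4%. The power penalty runs from none at rho 0 to 25% against 81% at rho 0.8, for a 0.8 SD shift. Those figures rest on normal data, equal SDs and an assumed rho; only the direction follows from the design. For sparse yes/no outcomes changing one way, chi-square gives p-values that are too small. The damage is confined to secondary inference, since tolerability and the main PK parameters are handled descriptively.

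**What to change.** Reword the test sentence in 9.2 to say:

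- Within-patient changes are tested with the paired t-test or, if not normally distributed, the exact Wilcoxon signed-rank test.
- Paired yes/no outcomes are tested with exact McNemar.
- Contrasts across the four doses use a within-patient method that keeps patients with incomplete doses, such as a mixed model with patient as random effect. Cochran Q is a poor choice: it needs complete data, and section 7.4.1 makes tolerability events themselves grounds for withdrawal, so it would drop the patients of most interest.
- Mann-Whitney and Fisher exact are kept for patient-level covariates, one value per patient, labelled exploratory.

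The cost is a few lines of text and no extra data or visits; the across-dose model needs a little more specification than the rest. One small downside should be accepted openly: with 8 patients, exact McNemar needs at least six one-way changes to fall below 0.05 (2 × 0.5⁶ = 0.031), so yes/no outcomes are better reported mainly as proportions, as section 9.1 already plans.
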